#### Power calculation

The primary expected outcome of the study is a lower dental caries experience in the intervention group, compared to the control group, after 24 months. A power calculation indicated that a sample of 330 children will be required (165 children in each group) to detect a minimum difference of 2 decayed, missing and filled surfaces (dmfs) between the intervention and control group. This calculation is based on the following parameters: 80% power, a significance level of 5%, a mean dmfs of 6.9 ± 6.2 in 6-year-old children in the Dutch population [26], an expected loss to follow-up of 20 and 15% excess to account for clustering in the analysis. Further analyses indicated that a sample of 330 children will be amply sufficient to detect differences in tooth brushing-related outcomes.

### The intervention

All children, in both the intervention and control group, will receive care as usual, consisting of regular dental check-ups, dental health education following the Ivory Cross national guideline, and if indicated, preventive treatment (fluoride varnish and/or fissure sealants) and/or caries treatment (fillings, non-restorative caries treatment or extractions) [27]. Regular dental check-ups for young children are generally scheduled every 6 months, or at shorter intervals when children are identified as having an increased caries risk. Key oral health messages of the Ivory Cross national guideline include twice daily tooth brushing with fluoride toothpaste (500–750 ppm fluoride), reducing the frequency of carbohydrate intakes to three main meals and a maximum of four (healthy) snacks per day, and avoiding foods and drinks before or during bed time [4]. In addition to care as usual, parents of children in the intervention group will receive supplementary support to adhere to the advice of twice daily tooth brushing with fluoride toothpaste, following the ‘Uitblinkers’ intervention.

#### Development and procedure of the intervention

The ‘Uitblinkers’ intervention has been developed by a working group of researchers with expertise in paediatric dentistry, dental public health, educational psychology, behavioural therapy and pedagogy. It also uses (modified) components of the Dutch ‘BeeBOFT’ programme: an intervention to improve parenting skills for the prevention of childhood obesity [28]. The intervention is a semi-structured interview between an OHP (dentist, dental hygienist or dental therapist) and a parent. The interview focusses on two components: ^1)^ identifying possible barriers that parents may experience with brushing their children’s teeth, and ^2)^ exploration of possible parenting strategies to tackle the identified barriers using principles from learning theory. The intervention consists of a two-day training for OHPs and a toolkit (semi-structured script and cards) to guide the interview.

A core principle of the interview method is to create a positive, non-judgmental collaborative conversation between the OHP and the parent. This is created through expression of empathy, asking open-ended questions and through the provision of patient-centered advice, rather than the traditional authoritarian approach which heavily relies on a directive style of counselling (‘blaming the victim’). Evidence shows that people are more intrinsically motivated to change their behaviour if they feel autonomous, connected and actively involved in the counselling process [29]. Therefore, OHPs will be trained in empowering parents and stimulating their involvement in finding a suitable approach to tackle barriers related to tooth brushing. Many of the aforementioned conversation techniques are interview and counselling principles that are also applied in motivational interviewing (MI) [30] and in Egan’s ‘Skilled Helper’ model [31].

To identify barriers to tooth brushing, the OHP starts the interview by first asking about positive experiences (e.g. “What is going well with brushing your child’s teeth?”). This is to empower the parent and to avoid negative sentiment. This is followed by open-ended questions about the moments when tooth brushing is challenging. The OHP encourages the parent to explore their own barriers by asking for an elaboration, explicit examples or more details of challenging situations. Then, the OHP shows a set of nine cards, with on the front side barriers to twice daily tooth brushing (in text and in illustrations). The nine barriers are based on scientific literature [8, 9] and include “Tooth brushing is challenging …”
“… when my child is heavily resisting or crying”“… when my child is too tired”“… when my child wants to brush by his/herself”“… because I don’t want to force my child against his/her will”“… when my child has pain”“… when it’s too busy (in the morning)”“… when it’s too busy (in the evening)”“… when I am tired”“… when I am stressed or pre-occupied”.

The cards and illustrations are designed to make parents aware of common barriers that are known to exist among parents, and to support the conversation especially for those who are low literate. The parent is subsequently asked to select the barrier he or she best identifies with.

After a barrier has been selected, the OHP and parent will discuss possible parenting strategies to address the specific barrier, whereby the OHP provides background information on the basics of stimulus control or operant conditioning in relation to tooth brushing. The strategies per barrier that are put forward by the OHP are described on the back-side of each card and summarised in Table 1. The OHP and parent aim to arrive at an agreed action plan, which will be documented for follow-up. Parents who are not able to name any barrier related to twice daily tooth brushing will be excluded from the study.

**Table 1 Tab1:** Possible approaches to address parental barriers to twice daily tooth brushing, based on principles from learning theory

Barrier	Principle	Approach (summary)
“Tooth brushing is challenging when…”		
My child is heavily resisting or crying	Operant conditioning/authoritative parenting	• Ensure that tooth brushing in practiced on a regular basis, using small steps and affirmations to build towards a cooperative atmosphere. • Make parents aware that if tooth brushing is skipped because the child does not cooperate, the child is being rewarded for this unwanted behaviour. Hence, the unwanted behaviour is reinforced and will tend to continue. • Explain to parents that tooth brushing should happen at all times, even when the child is being uncooperative. Negative unwanted behaviours can be extinguished by ignoring them. Parents can gradually work towards a more cooperative atmosphere through a step by step approach (e.g. first brushing only two teeth), the use of compliments, and retaining a positive and calm attitude.
My child is too tired	Stimulus control	• Try to intervene before the unwanted behaviour occurs. • Ensure that tooth brushing is done before the child gets tired, by creating a predictable and efficient routine in the evening. • Make parents aware that children can become hyperactive and unmanageable when they are tired, which makes tooth brushing more challenging. • Help parents to think along how tooth brushing can be moved earlier in the evening, for example through a more efficient evening routine (e.g. already setting the table, or preparing foods), or by placing tooth brushing earlier in the sequence of evening activities (e.g. immediately after dinner).
My child wants to brush by his/herself	Operant conditioning/Chaining	• Make tooth brushing a collaborate activity; ensure that the parent retains control and that the child feels more autonomous. • Explain to parents how tooth brushing can be made into a collaborative activity: break the tooth brushing activity into small steps; allow the child to perform the simple steps (e.g. putting water in a cup, applying toothpaste on the brush); perform the actual brushing activity together while describing each step to the child; give compliments. The child is gradually allowed to perform more steps by itself. • Emphasise that the parent should always re-brush the child’s teeth.
I don’t want to force my child against his/her will	Operant conditioning/authoritative parenting/role modelling	• Ensure that tooth brushing in practiced on a regular, daily basis; the parent can function as a role model. • Make parents aware that if tooth brushing is skipped because the child does not want to brush, the child learns that tooth brushing can be avoided by saying no. Hence, this non-cooperative behaviour will be reinforced. • Explain to parents that tooth brushing should happen at all times, even when the child does not want to. If tooth brushing becomes a fact, children lose their motivation to argue. Parents can set a good example by letting the child copy the parent when brushing teeth and by giving compliments. Herewith, tooth brushing becomes a more fun and joint activity, which gradually reduces uncooperative behaviour.
My child has pain	Operant conditioning/authoritative parenting	• In case of actual pain (gingivitis; exfoliating teeth): Ensure that the painful/inflamed area is brushed twice a day with a soft tooth brush. Avoiding tooth brushing may worsen the pain. • In case of imaginary pain: Explain to parents that tooth brushing should happen at all times. Teach the child to deal with the pain, and let the child gradually experience that brushing is not as painful as they might have imagined, by building up tooth brushing in small steps (e.g. first brushing only two teeth or a not painful area in the mouth) and by giving compliments and praise.
It’s too busy (in the morning)	Stimulus control	• Help parents to structure time and space. • Ensure that tooth brushing is built into daily, activities, as a routine, creating a predictable and stable pattern in the morning. • Help parents find a moment in the morning where tooth brushing fits best in their sequence of activities and locations (e.g. in the bathroom before breakfast, in the kitchen after breakfast). • Advice parents that time can be saved by good preparations (e.g. already preparing the school lunch box in the prior evening).
It’s too busy (in the evening)	Stimulus control	• Help parents to structure time and space. • Ensure that tooth brushing is built into daily activities, as a routine way, creating a predictable and stable pattern in the evening. • Help parents find a moment in the evening where tooth brushing fits best in their sequence of activities and locations (e.g. immediately after dinner, before bedtime reading). • Make parents aware that tooth brushing becomes challenging once children are, for example, watching TV. Preferably tooth brushing is done before leisure time. Help parents to introduce ground rules and to apply them consistently.
I am tired	Stimulus control	• Ensure that tooth brushing is practiced on a regular basis as a routine. • Explain to parents that routines and regularity increases predictability of the behaviour, which reduced unwanted/uncooperative child behaviour and takes less energy from the parent.
I am stressed or pre-occupied	Authoritative parenting	• Ensure that stress from the parent is not transferred to the child, by staying calm and positive during the tooth brushing and bed time routine. • Explain to parents that children feel the stress of a parent (e.g. parents raising their voice, becoming a bit hard-handed). Children often respond to stress by copying the behaviour (e.g. shouting, showing resistance). This will make tooth brushing more challenging. • Advice parents to stay calm, not to raise their voice and to keep the atmosphere positive in order to facilitate tooth brushing for the child. The stress of the parent should not become the stress of the child.

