#### Children and their parent(s)

Each dental practice, both in the intervention and control group, will recruit a sample of at least ten 3 to 4-year-old children from their own patient population for inclusion in the study, using a simple random sampling method. Eligible children will be listed from the patient registry and given a random number by the coordinating dental therapist, using the website http://random.org. Subjects will be approached in numerical order until at least ten subjects are included. In cases of twins, only one child of the family will be selected. Children will be eligible to participate if they are healthy (ASA classification I) and between 36 and 59 months old at the time of inclusion. Exclusion criteria are:
Children with a physical or mental disability,Children with a high caries activity (decayed, missing and filled teeth (dmft) ≥ 4), based on the patient dental record,Children with hypomineralised second primary molars,Children (or siblings of the child) who have been receiving treatment at a referral practice for paediatric dental care,Children of parents who do not speak and understand the Dutch language.

Three to 4-year-olds are selected for two reasons. First, the restriction of the age group reduces variation in dental caries levels, allowing better comparison of the intervention’s effect. Second, children are preferably targeted from a young age when oral health behaviours are still shaped and more amendable to change. However, in The Netherlands only 35% of two-year-olds are visiting the dentist, which increases to 95% when children reach the age of four [25]. Therefore, the choice was made to include 3 to 4-year-old children, increasing the number of young children that can be reached. Parents will be informed about the study aim and procedures, privacy and confidentiality regulations and their rights to withdraw at any time using an information letter (Additional file 1). Prior to participation, written informed consent will be obtained from the parents by the dental therapist.

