#### Contact moments

The study consists of five contact moments for parents in the intervention group:
T0.0: baseline - visit to the dental practice:Baseline data collection; first interview, including identification of a barrier, discussion of a possible strategy and agreement on an action point.T0.1: 1 month after T0.0 - visit to the dental practice (parent only):Second interview, including follow-up on the progress with the first action point, identification of a second barrier (if present), discussion of a possible strategy and agreement on a second action point.T0.2: 1 month after T0.2 – telephone recall:Telephone recall to follow-up on the progress with the first and second action points.T1: 6 months after T0.0 – visit to the dental practice:Follow-up data collection.T2: 24 months after T0.0 – visit to the dental practice:Follow-up data collection.

Where possible, the research visits at the dental practice will be combined with a regular dental check-up. Parents in the control group will visit the dental practice only at T0.0, T1 and T2 for baseline and follow-up data collection. The interval between T0.0 and T1 is allowed to deviate by 2 months, and the interval between T1 and T2 may vary with 3 months. If parents miss their appointment at T1 and T2, or at T2 only, they will be treated as dropouts. If they only miss the appointment at T1, missing data for T1 will be imputed. Missed telephone recalls will be documented to account for this in the analysis.

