#### Measures of fidelity

Fidelity is defined as the extent to which delivery of an intervention adheres to the protocol originally developed [38]. To measure fidelity, dental therapists in the intervention group will be requested to document the selected barriers and action points of participants. Questions on the implementation of the intervention are included in the questionnaire and focus group interview with dental therapists (see Additional files 2 and 3). In addition, the 20 parents who will be contacted for a telephone interview will be asked to give a description of their research visit, to determine whether the study protocol was followed as intended.

To assess whether the target group is reached, dental therapists in both intervention and control practices will be requested to document the number of subjects that agreed to participate out of the number of eligible subjects that were approached, as well as reasons not to participate. Non-participating parents will be asked two questions on their highest completed level of education and country of birth, to be able to assess potential selection bias.

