### Statistical analysis

All data will be coded with a unique ID, and data will be securely stored at the Department of Social Dentistry at ACTA. The analysis will be performed in STATA. Differences in the primary outcome (dmfs and the combined ICDAS scores ‘B and C’ and ‘A, B and C’) between children in the intervention and control group at T2 will be analysed using zero-inflated Poisson or negative binomial regression. Baseline differences in children’s dmft scores (obtained from dental records) will be taken into account.

Differences in the three tooth brushing-related outcomes between children in the intervention and control group at T1 and T2 will be analysed using ordered logistic or logistic regression (for tooth brushing frequency in children; either treated as a ordinal variable or dichotomous variable, depending on the distribution of responses), and linear or negative binomial regression (for parental self-efficacy scores and children’s plaque scores).

All analysis will be adjusted for clustering of observations within dental practices. In case of significant differences in co-variates (moderators) between the intervention and control group at baseline (T0), the analysis will be adjusted accordingly for these co-variates, or in case of sufficient power, a sub-group analysis will be performed. An intention-to-treat analysis will be conducted to account for participants that will be lost to follow-up. Statistical significance is set at α = 5%.

Qualitative data from the focus group interviews and telephone interviews will be processed using the Maximised Qualitative Data Analysis programme (Verbi-software MAXQDA). Conventional content analysis will be used to identify emergent themes and concepts related to the feasibility and acceptability of the intervention.

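### Parents who cannot name a brushing barrier are excluded, but only intervention parents are asked, so the two groups become different populations after enrolment

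*Protocol article*

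**What the plan says.** Under *Children and their parent(s)*, both groups recruit in the same way: a simple random sample from the practice registry, one list of five exclusion criteria, and consent first ("Prior to participation, written informed consent will be obtained from the parents by the dental therapist"). Inability to name a barrier is not on that list.

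The criterion appears later, under *Development and procedure of the intervention*, after the account of how barriers are elicited with open questions and nine cards: "Parents who are not able to name any barrier related to twice daily tooth brushing will be excluded from the study".

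*Contact moments* places that interview at T0.0 ("Baseline data collection; first interview, including identification of a barrier, discussion of a possible strategy and agreement on an action point"), in a schedule introduced by "The study consists of five contact moments for parents in the intervention group". For the other group it says: "Parents in the control group will visit the dental practice only at T0.0, T1 and T2 for baseline and follow-up data collection". *Measures of fidelity* adds that "dental therapists in the intervention group will be requested to document the selected barriers and action points of participants"; no such record is described for controls.

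On the analysis set, *Statistical analysis* says: "An intention-to-treat analysis will be conducted to account for participants that will be lost to follow-up".

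**The concern.** Two groups recruited under identical criteria are then filtered differently, by something that happens inside the intervention. Intervention families stay in only if the parent names a barrier. Control families stay in regardless.

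Barriers are not a neutral characteristic here. The section on the 'Uitblinkers' intervention sets out a chain from coping with barriers through parental self-efficacy, brushing and plaque to caries. Selecting on barriers in one group therefore affects the primary outcome and all three secondary outcomes. If families without barriers have less caries, the easy brushers remain only among the controls, and a working intervention could be judged a failure. The trial already concedes selection bias at practice level in its Discussion; this adds an avoidable selection at family level.

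**Working it through.** **Can a control parent meet the criterion?**

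| Step | Intervention | Control |
|---|---|---|
| Sampling, listed exclusions, consent | Yes | Yes, identical |
| Baseline data at T0.0 | Yes | Yes |
| Interview asking for a barrier | Yes, at T0.0 | None described |
| Barrier documented by therapist | Yes | None described |
| Can be excluded for naming none | Yes | No occasion to be |

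The nearest item asked in both groups is the self-efficacy questionnaire. It asks about confidence in nine given situations; it does not ask parents to name a barrier and triggers no exclusion.

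**The plan's own sample size.** With a difference of 2 dmfs, SD 6.2, 80% power and a one-sided 5% test, n = 2 × [6.2 × (1.645 + 0.842) / 2]² ≈ 119 per group. Then 119 × 1.20 × 1.15 = 164.2, rounded up to 165, so 330 in total. A two-sided test gives 151 per group before inflation and does not reproduce 330. The present point does not depend on this, but the inflation covers only loss to follow-up and clustering, not barrier exclusions.

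**Size of the shift with no true effect.** Let p be the share of parents naming no barrier, r the ratio of their children's mean dmfs to that of the other children, and 6.9 the overall mean (planning value from *Power calculation*). The control group keeps the mix, with mean 6.9. The intervention group keeps only barrier families, with mean 6.9 / [(1 − p) + p·r]. Neither p nor r is in the document; the values below are assumptions.

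| p | r | Intervention mean | Shift | Share of 2 dmfs |
|---|---|---|---|---|
| 0.02 | 0.7 | 6.9/0.994 = 6.94 | +0.04 | 2% |
| 0.05 | 0.7 | 6.9/0.985 = 7.01 | +0.11 | 5% |
| 0.10 | 0.7 | 6.9/0.97 = 7.11 | +0.21 | 11% |
| 0.20 | 0.5 | 6.9/0.90 = 7.67 | +0.77 | 38% |
| 0.30 | 0.5 | 6.9/0.85 = 8.12 | +1.22 | 61% |

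A plus sign means the intervention looks worse. If r exceeds 1 the sign reverses: p = 0.10, r = 1.3 gives 6.9/1.03 = 6.70, a shift of −0.20.

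The same quantity can be written as p × D, with D the difference in mean dmfs between families with and without a barrier. For p from 5% to 30% and D from 1 to 4 dmfs, this runs from 0.05 to 1.2 dmfs.

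**Against the success criterion.** *Outcome measures* requires a 25% reduction, put at 1.5 to 2.0 dmfs. Take p = 20% and D = 3: a true reduction of 2 dmfs in the retained families appears as 2 − 0.6 = 1.4, below that range. In relative terms, which do not depend on the 6.9, a true 25% reduction appears as 1 − 0.75/0.97 = 23% at p = 0.10, r = 0.7, and as 1 − 0.75/0.85 = 12% at p = 0.30, r = 0.5.

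**Against power.** Removing both allowances leaves 165 / (1.20 × 1.15) ≈ 120 children per group. Two-sided power for an apparent difference of 2.0, 1.8 (p = 10%, D = 2) or 1.4 dmfs is about 70%, 61% and 42%; one-sided, about 80%, 73% and 54%.

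**The case against.** The strongest reply concerns size. The interview presses for a barrier and then shows nine cards that include everyday situations such as tiredness or a busy morning. Few parents may fail to pick one, and at 2–5% the shift is about 0.04 to 0.11 dmfs. The base of 6.9 is a general-population mean at age 6, while the trial excludes children with dmft of 4 or more, so the absolute shift is probably smaller still. Both points are fair. They bear on magnitude; the asymmetry remains.

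Direction is also open. Parents who deny any barrier may be giving socially desirable answers, or may be less aware, and their children could have more caries. That stands: a bias against the intervention is the likelier case, not an established one.

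Adjustment helps in part. Baseline dmft is taken into account, and self-efficacy, brushing frequency and plaque are measured at T0.0 in both groups, so some imbalance would be visible and some absorbed. But barrier status is not recorded in controls, so the control families who would have been excluded cannot be identified. Matching on practice size and regional SES does not address it. Replacing excluded families to reach ten per practice restores numbers, not comparability.

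On the text, the exclusion sentence names no group, the order of steps within T0.0 rests on how they are listed, and the additional files are not shown. Yet the article describes no barrier question for controls, and the exclusion follows consent whichever step comes first. Finally, the intention-to-treat sentence speaks only of loss to follow-up. Even so, an analysis that drops enrolled families because of what they said in the intervention interview does not keep participants as assigned.

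**Conclusion.** The concern holds and should be fixed before analysis. As written, the rule excludes families after consent, in one group only, on a variable that the trial's own model ties to its outcomes, and it is inconsistent with an intention-to-treat set. This conclusion rests on the text and needs no assumption about numbers.

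The size does need assumptions. With 10–30% of parents naming no barrier, a caries ratio of 0.5–0.7 and a mean of 6.9, the shift is 0.2 to 1.2 dmfs (3–18% of the mean, 11–61% of the target difference), before any adjustment for baseline dmft. It is smaller if few parents fail the question, and it changes sign if their children have more caries than the others.

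**What to change.** Delete the exclusion sentence under *Development and procedure of the intervention*. State that every enrolled intervention family stays in follow-up and in the primary analysis. Where a parent names no barrier there is no action point, and this is recorded as fidelity data. The cost is protocol wording, plus a slight dilution of the average effect because some families have no barrier to work on.

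If a population with barriers is wanted, ask the same barrier question in the same way of parents in both groups before inclusion, and list it with the eligibility criteria under *Children and their parent(s)*. This costs one screening question in control practices and some extra recruitment in both groups. For scale, ending with 165 per group would take 165/0.95 ≈ 174 to 165/0.70 ≈ 236 families screened per group if 5–30% name no barrier.

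Should any families already have been excluded under the rule, follow them up where consent allows and analyse them in the intervention group; that would cost more than wording, since it means re-contact and the 24-month examination. Report how many there were in any case.
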